## Abstract

**Background:**

Virtual Reality Exposure Therapy (VRET) is found to be a promising and a viable alternative for in vivo exposure in the treatment of specific phobias. However, its usefulness for treating dental phobia is unexplored. The aims of the present study are to determine: (a) the efficacy of VRET versus informational pamphlet (IP) control group in terms of dental trait and state anxiety reductions at 1 week, 3 months and 6 months follow-up (b) the real-time physiological arousal [heart rate (HR)] of VRET group participants during and following therapy (c) the relation between subjective (presence) and objective (HR) measures during VRET.

**Methods:**

This study is a single blind, randomized controlled trial with two parallel arms in which participants will be allocated to VRET or IP with a ratio of 1:1. Thirty participants (18-50 years) meeting the Phobia Checklist criteria of dental phobia will undergo block randomization with allocation concealment. The primary outcome measures include participants’ dental trait anxiety (Modified Dental Anxiety Scale and Dental Fear Survey) and state anxiety (Visual Analogue Scale) measured at baseline (T0), at intervention (T1), 1-week (T2), 3 months (T3) and 6 months (T4) follow-up. A behavior test will be conducted before and after the intervention. The secondary outcome measures are real-time evaluation of HR and VR (Virtual Reality) experience (presence, realism, nausea) during and following the VRET intervention respectively. The data will be analyzed using intention-to-treat and per-protocol analysis.

**Discussion:**

This study uses novel non-invasive VRET, which may provide a possible alternative treatment for dental anxiety and phobia.

**Trial registration number:**

ISRCTN25824611, Date of registration: 26 October 2015.

## Background

It is estimated that as many as 75 per cent of US adults experience some degree of dental anxiety, from mild to severe [1, 2] and that 50-60 % of individuals suffer from a specific fear of dental procedures and dental related stimuli [3]. Given that dental phobia belongs to the most common phobic conditions in our society, finding a suitable specific non-invasive strategy to reduce dental anxiety and treat dental phobia is both warranted and important.

Exposure based treatment programs are considered as the gold standard in the treatment of specific fears and phobias [4–6], including those related to the dental treatment situation [7], [8, 9]. However, potential drawbacks include: (a) the difficulty for patients to mentally visualize the anxiety inducing threat as in imaginal exposure therapy [10], (b) the unwillingness of patients to face the actual threat in in vivo exposure therapy (IVET) resulting in refusal or termination of therapy accounting for 25 % [11], (c) the failure to achieve clinically significant symptom relief, and return of fear, following exposure therapy [12], (d) the poor availability of psychological services [13] and (e) the high costs [14] involved with this treatment.

Recently, VRET has become a viable alternative for in vivo exposure in the treatment of fears and specific phobias [15] including claustrophobia [16], acrophobia [17], fear of flying [18], and spider phobia [19]. This involves conducting exposure therapy using computer generated Virtual Reality (VR) environments by systematic confrontations of patients with their potentially fear-provoking (i.e., ‘conditioned’) stimuli so that habituation occurs [15, 17]. Compared to IVET, VRET is safer because the patients faces the virtual representation of their threat more gradually in a controlled manner, and at their own pace [10]. As the entire exposure process in VRET is completed under privacy of therapists’ office it may elicit less fear of social embarrassment to the patients [20] . VRET can be repeated, whenever and, for as many times [10] as necessary without incurring any additional costs. In-vivo exposure therapy requires training on the part of therapist and is usually delivered by trained psychologists. Compared to this, administration of VRET may just require a working knowledge of computer operation and basic training to operate the apparatus.

VRET is known to elicit a feeling of being “present” in the virtual environment [15, 17]. This sense of presence is considered to be the essence for the effectiveness of VR [21] and has been found to be an important mediating variable [15] between the VR media and the level of anxiety induced [22]. Presence in VR is measured subjectively with questionnaires or objectively with physiological measures [e.g., heart rate (HR), body posture, skin conductance level] [15, 17]. VRET was found to be able to elicit physiologic responses in individuals with fear of flying phobia (measured by HR and skin-conductance) when exposed to VR flights, and these responses decreased following repeated VR exposure flights [23]. Psychophysiological arousal forms the basis for an effective exposure based therapy [24]. A recent systematic review has suggested that VRET does elicit psychophysiological arousal, thereby rendering it to be a promising treatment modality for treatment of anxiety disorders [25]. However, the effect of VRET on HR is inconclusive because of limited well designed studies [25]. Also, there is no published research examining the role of VRET in causing psychophysiological arousal in anxious dental patients. Further, studies examining the relationship between subjective presence and physiological responses are limited [26].

A recent meta-analysis suggests VRET to be slightly, but significantly, more effective than IVET (in vivo exposure therapy) [27]. Although, VRET provides a powerful means of modifying affect, because of its immersive nature, it has not been tested yet as a therapy for dentally related anxiety or dental phobia. In an effort to answer this question, we will use VRET simulation software for the treatment of dental phobia and test its efficacy in the present study. The primary objective of the present study is to determine the efficacy of VRET versus an informational pamphlet control group in terms of dental trait and state anxiety reductions at 1 week, 3 months and 6 months follow-up among a sample of patients suffering from dental phobia. The secondary objectives are to determine (a) the real-time effect of VRET on the course of participant’s physiological response (HR) on exposure with a series of dentally related cues during therapy and (b) the relation between subjective (i.e., presence) and more objective (i.e., HR) measures during VRET. It is hypothesized that: (a) VRET would result in a significantly reduced level of dental trait anxiety [measured by MDAS (Modified Dental Anxiety Scale) and Dental Fear Survey (DFS)] and state anxiety [indexed by VAS-A (Visual Analogue Scale-Anxiety)] at 1 week, 3 months and 6 months follow-up compared to the informational pamphlet control group, (b) VRET would result in significantly higher reduced physiological arousal (i.e., HR) to dental anxious stimuli/cues relative to the baseline HR values following therapy, (c) VRET will demonstrate a positive correlation between subjective and objective measures of ‘presence’.

## Methods

### Trial design

The study will be conducted in compliance with local regulations and internationally established principles of the declaration of Helsinki (64^th^ World Medical Association General Assemble, Fortaleza, Brazil, 2013). The study and protocol were approved by the Ethics Commission of the SEGi University (Reference: EC01/14-01). This VRET study will be designed as a single blind (Biostatistician will be blinded), randomized controlled trial with two parallel arms: VRET and Informational Pamphlet (IP) groups with an allocation ratio of 1:1 as shown in Fig. 1. Thirty participants undergo block randomization so that we have equal distribution of participants in both the groups. In order to preserve the allocation concealment, we will be using, sealed, opaque, sequentially numbered envelopes (SNOSE); [28]. Envelopes will be opened serially (next highest number) only after the participant details (patient unique number, date and patient signature) are entered on the envelope. Carbon paper inside the envelope enables transfer of details to the assignment card. Cardboard or aluminum foil inside the envelope renders the envelope impermeable to intense light [29].

**Fig. 1 Fig1:**
[figure not shown]
Participant flow and timing of evaluation

The two groups are assessed at baseline (T0), before and after intervention (T1), at 1-week follow-up (T2), 3 months after treatment (T3) and 6 months after treatment (T4) on a set of variables that are linked to the various research questions. The participant flow and timing of evaluation is depicted in Fig. 1.

### Participants

Adult outpatients who have not visited the dentist since last 12 months or those reporting with anxiety and avoidance of dental procedures will be screened and recruited from the outpatient service of Oral Health Centre of faculty of Dentistry, SEGi University at Malaysia. The trial process starts with a short self-report assessment with a MDAS questionnaire to screen for possible dental phobia. Interested participants, who agreed to participate in our VRET Dental Phobia study, with a MDAS score of ≥15, will be contacted and given an appointment by the researcher for an interview. A screening tool, the “Phobia Checklist” [30] will be used for the assessment of dental phobia in this study. This measure for assessing dental phobia has previously been validated against the Structured Clinical Interview for DSM-IV with a sensitivity of 0.95, specificity of 0.99, and an overall hit rate of 97 %. The phobia checklist consists of four questions based on the DSM-IV-TR [31]criteria for specific phobia. The patients are requested to mark either a ‘YES’ or ‘NO’ response to the following questions related to their dental anxiety:The sight of the feared object or experiencing the situation evokes an excessive fear response.The fear is greater than justified.Avoidance or giving up things because of the fear.Avoidance of the situation or object causes daily impairment.

An individual is categorized as dental phobic only upon answering ‘YES’ against all four questions of the phobia checklist. In the present study, the checklist will be administered during the screening interview and at 6 month follow-up.

Anticipated timeline for this study will be as follows:Enrollment to Inclusion Interview: Maximum 1 week.Inclusion Interview to Baseline, Randomization & Allocation: Maximum 1 week.Baseline, Randomization & Allocation- Intervention: Maximum 1 week.

### Eligibility criteria

#### Inclusion criteria

Participants should satisfy all criterion for inclusion.Meeting the criteria of “Phobia checklist”.An age between 18 to 50 yr.Any dental phobic patient requiring the following planned dental treatment/s of *at least* 30 minutes per appointment.Restorative dental procedure which may or may not be requiring local anesthesia.Extraction procedure requiring local anesthesia.

The participants will be recruited from the out-patient department of the oral health Centre where it is mandatory for every patient to undergo a diagnostic examination. The information about treatment needs will be obtained from the findings of the diagnostic examination.

#### Exclusion criteria

Presence of any criteria mentioned below result in exclusion of the participant.Hearing or visual impairment such as stereoscopy blindness or nystagmus.Known mental disorders such as psychosis, post-traumatic stress disorder, developmental or intellectual disability and cognitive impairment.Known balance disorders such as vertigo and cybersickness.Patients with previous history of epileptic seizures.Any history of cardiac problems.Patients who are undergoing, or have undergone, any cognitive behavioral therapy (CBT)-based intervention for dental phobia.Language impediment (cannot understand English).Patients wearing glasses of greater than plus 3.5 power.

### Outcome measures

Table 1 and 2 provide an overview of the measures at various time points. Participants of both groups are evaluated using a series of measures as mentioned below. The participants of the VRET group will undergo HR monitoring in real time, assessed for subjective discomfort/distress and evaluated for VR experience at T1 during the intervention as depicted in Table 1 and 2.

**Table 1 Tab1:** Showing overview of measures at different time periods

		Measurements						
		Primary outcome				Secondary outcomes (Only with VRET)		
		State anxiety (VAS-A)	Trait anxiety (MDAS)	Dental Fear Survey(DFS)	Behavioral test	Physiological parameter (HR)	Subjective Unit of Distress Scale (SUDS)	VR experience
Baseline (T0)	Screening interview	X	X	X	-	-	-	-
Intervention (T1)	Preoperative interview	X	X	X	X	-	-	-
	VRET^a^ session or IP^b^	-	-	-	-	X	X	X
	Postoperative interview	X	X	X	X	-	-	-
Follow-up (T2,T3)	E mail	X	X	X	-	-	-	-
Follow-up (T4)	E mail	X	X	X	-	-	-	-

Note: ‘X’ Indicates timing of measurement of the outcome measures

^a^VRET: Virtual Reality Exposure Therapy

^b^IP: Informational Pamphlet

**Table 2 Tab2:** Showing measures during VRET session

Measures		VRET session																											
		Baseline phase (10 min)	Training phase (2 min)	Experimental phase(Sessions repeated p,q,r,s,t times until SUDS score ≤2)																									Immediate Post-therapy phase (10 min)
				Scenario #1 (Idle)					Scenario #2 (Mirror)					Scenario #3 (Syringe)					Scenario #4 (Drill with no sound)					Scenario #5 (Drill with sound)					
1	Number of exposures			1	2	3	4	p	1	2	3	4	q	1	2	3	4	r	1	2	3	4	s	1	2	3	4	t	X
2	Subjective measure(SUDS)			X	X	X	X	X	X	X	X	X	X	X	X	X	X	X	X	X	X	X	X	X	X	X	X	X	X
3	Subjective measure(Presence)			X	-	-	-	-	X	-	-	-	-	X	-	-	-	-	X	-	-	-	-	X	-	-	-	-	X
4	Subjective measure(Realism)			X	-	-	-	-	X	-	-	-	-	X	-	-	-	-	X	-	-	-	-	X	-	-	-	-	X
5	Subjective measure(Nausea)			X	-	-	-	-	X	-	-	-	-	X	-	-	-	-	X	-	-	-	-	X	-	-	-	-	X
7	Objective measure(HR)	X	X	X	X	X	X	X	X	X	X	X	X	X	X	X	X	X	X	X	X	X	X	X	X	X	X	X	X

Note: ‘X’ Indicates timing of measurement of the outcome measures

#### Primary outcome measures

##### Anxiety

Will be determined utilizing VAS-A, MDAS and DFS survey.Visual analogue scale for state anxiety (VAS-A) [32]. VAS-A will be recorded by asking the participants to draw a cross mark (X) on a 0-100 mm horizontal scale with the extreme left edge of the scale indicating feeling totally calm and relaxed (0) and the extreme right edge, feeling the worst fear imaginable (100). The measured distance from the left edge of the line to the cross mark placed by the participants to the nearest millimeters provides a quantitative variable that can be used in statistical analysis. The VAS-A has been found to be a simple, sensitive, fast, reliable and valid tool to measure level of state anxiety [33].Modified Dental Anxiety Scale [34]. The Modified Dental Anxiety Scale (MDAS; Humphris 1995) is a 5-item scale assessing dental (trait) anxiety. Respondents are asked to rate their level of anxiety across five different scenarios (e.g., anxiety response on a previous day to a prospective dental visit, when in the waiting room, when about to have tooth drilled, teeth scaled and injection to the gums) on a 5-point Likert scale ranging from “not at all anxious” to “extremely anxious”, and possible scores range from 5 to 25, with greater scores indicating higher level of dental anxiety. The MDAS shows high levels of internal consistency and good construct validity [35].Dental Fear Survey [36]. The Dental Fear Survey (DFS; Kleinknecht 1973) is a 20-item measure used to identify emotional and physiological reactions associated with several aspects of dentistry, as well as avoidance of dental care due to anxiety. Possible scores range from 20 to 100, with greater scores indicating higher levels of dental anxiety. The DFS has established reliability, validity and sensitivity [37].

##### Behavioral avoidance test

A Behavioral avoidance test will be done prior to, and immediately after, the interventions at T1 by means of standardized observation of behaviour, and an interview for both the groups. The test is similar to the VRET scenarios, and provides a baseline behavioral assessment measure to compare the responses of the patient before and after the VRET. This in vivo test represents an observer-rated instrument earlier used by Doering et al. [38]. It contains 5 situations that occur during a dental visit (e.g., sitting in the dental chair, inspection of the oral cavity using dental mirrors, approaching dental syringe, approaching dental drill without sound and approaching dental drill with sound). While the patient undergoes the dental visit it is observed whether he/she is able to tolerate the situation, and he/she is asked by the observer to assess his/her level of anxiety on a scale of 0–10 in each situation. Both observation and answers to the standardized questions are recorded during the procedure.

#### Secondary outcome measures

Psychophysiological parameter: A heart rate wrist band will be used to record the real time response to VRET at T1 during VRET session. The device will be integrated with the VR software and the output will be recorded during therapy.Subjective Units of Distress (SUD) scale: The SUD scale is an eleven-point scale [39] to measure the intensity of subjective distress currently experienced by an individual. It is used by the therapist in desensitization based therapies as a standard to evaluate the progress of the therapy. Typically the patient is asked by the therapist “On a scale of 0-10 where, 0 is no discomfort and 10 is the worst, how do you feel right now”. The researcher will record the SUDS scores during each VR scenario exposure of the VRET session. During the VRET session each VR exposure is repeated, until there is habituation demonstrated by a relatively low SUD score (≤2), and the next scenario is introduced. The total number of VR exposures with each VR scenario that was required to achieve SUDS score of ≤2 will be summed up and recorded by the researcher post-therapy.VR experience: will be evaluated at T1.Time perception is determined by asking the participants to calculate approximately the duration of VR immersion with therapy [40] and the ratio of subjective and objective duration will be evaluated.Presence will be measured using an 11-point verbal rating scale (VRS) [41].Realism will be indexed with an 11-point (VRS) [41].Severity of nausea (‘cybersickness’) will be measured using an 11-point VRS [41].Intention to use VR goggles again will be indexed with a yes/no response.Intention to revisit the dental surgery will be measured with a yes/no response.

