Only verbal guidance and exposure techniques will be used on the participants during VRET. There will be no relaxation or other CBT-based interventions during therapy. Participants will be instructed to become as involved as possible and focus on their most frightening stimuli of the particular part of the virtual environment (describing the situation, any strange sensations and their feelings). This will be done to avoid dissociation from the VR experience. During the simulated treatment, real-time recording of the psychophysiological parameters (HR) will be determined to obtain more ‘objective’ measures of the physiological state of the participants during therapy. The HR responses obtained with different cues (Idle, Mirror, Syringe, Drill with no sound and Drill with sound) in this phase will be compared with the baseline phase (No display) to study the HR variations. The subjective measures of presence, realism and nausea (cybersickness) are recorded following the 1^st^ exposure of each VR scenario as shown in Table 2.

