## Data analysis

The analyses will be performed based on the Consolidated Standards of Reporting Trials (CONSORT) statement regarding e-health [47]. An independent biostatistician will carry out the statistical analysis using SPSS 20.0.The recorded data will be labelled so that the biostatistician will not be able to distinguish between the two groups. All data will be analyzed using an intention-to-treat analysis. We will also conduct a per protocol analyses. Descriptive statistics will be calculated, whereas discrete variables will be summarized by frequencies or proportions. Continuous variables will be reported as means and standard deviations or medians and range (depending on the measurement level of the variables). Data will be checked for differences at T0, T1, T2, T3 and T4 between the VRET and informational pamphlet group using independent samples t-test. Between-group changes at post treatment will be calculated by using a 2 (pre-treatment/post-treatment) × 2 (VRET/Informational pamphlet) repeated measures MANOVA. Post hoc comparisons will be applied if clarification of the main effects of the MANOVA is needed. Effect sizes between the groups will be calculated with Hedges’ g. Clinical significance change analyses as described by Jacobson and Truax [48] will be conducted to determine whether the changes from pre-test to post-test are clinically significant [48]. Missing data analysis will be performed and the reason for non-adherence will be registered.

The continuous monitoring of HR data will help us determine whether the physiological changes diminish following multiple exposures with each scenario (suggestive of habituation-Reliability of therapy).

To evaluate the correlation between subjective measures of VR experience (presence, realism, nausea) with objective measure of HR during each VR scenario, only the first exposure measures will be considered to eliminate the order effects as shown in Table 2.

Since the baseline physiology levels will vary widely between individuals, we will be determining the percentage change from baseline HR during the first exposure of each VR scenario for analyses rather than considering the absolute values. The percentage change of heart rate (%HR) will be calculated as follows:$$ \%\mathrm{H}\mathrm{R} = \left(\mathrm{MeanVR} - \mathrm{MeanBaseline}\right)/\mathrm{MeanBaseline}, \times 100 $$where,

MeanVR: Mean of HR during the VRET of 1^st^ exposure of each VR scenario, and

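### Hypothesis (b) credits VRET with lower heart-rate arousal after therapy, but heart rate is recorded only in the VRET arm and compared only with each participant's own baseline

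*Protocol article*

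**What the plan says.** All places are in the Protocol article.

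- **Who is measured.** Outcome measures: "The participants of the VRET group will undergo HR monitoring in real time". Table 1 places HR, SUDS and VR experience under "Secondary outcomes (Only with VRET". Secondary outcome measures agrees: "A heart rate wrist band will be used to record the real time response to VRET at T1 during VRET session". The section on the informational pamphlet group describes no HR recording.
- **What is claimed.** Hypothesis (b) in Background: "VRET would result in significantly higher reduced physiological arousal (i.e., HR) to dental anxious stimuli/cues relative to the baseline HR values following therapy". Secondary objective (a) in the same section concerns "the real-time effect of VRET on the course of participant’s physiological response (HR) on exposure with a series of dentally related cues during therapy".
- **What HR is compared with.** Experimental phase: the responses to the cues "will be compared with the baseline phase (No display) to study the HR variations". That baseline is ten minutes with the headset off (Baseline phase).
- **How a decline will be read.** Data analysis: continuous monitoring is to show "whether the physiological changes diminish following multiple exposures with each scenario (suggestive of habituation-Reliability of therapy".
- **What both arms undergo.** The Behavioral avoidance test is given before and directly after the intervention at T1, by "standardized observation of behaviour, and an interview for both the groups". Its five live situations parallel the five VR scenarios. Table 1 marks no HR in either of those two rows.

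**The concern.** Hypothesis (b) is worded as a treatment effect, while the data behind it are a before/after comparison in one arm. HR can fall during a long session for reasons unrelated to VRET: the participant lies supine, becomes used to the room, and recovers from arousal on arrival. Table 1 also puts the pre-intervention avoidance test, with live syringe and drill, ahead of the VRET session, so the baseline HR itself may be raised and a later fall may be recovery. Without HR from pamphlet participants, none of this can be separated from VRET.

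At stake is a published statement that VRET lowers physiological arousal to dental cues, resting on data that would look the same if it did not. Background itself describes the evidence on VRET and HR as inconclusive for want of well-designed studies.

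**Working it through.** **1. Claim against data.**

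| Element | Hypothesis (b) | What is collected |
|---|---|---|
| Cause named | VRET | No unexposed comparator for HR |
| Time | After therapy | During the session, plus a 10-minute recording afterwards |
| Stimulus | Dental cues | VR cues; %HR is defined for the first exposure of each scenario only |
| Reference | Baseline HR | Own black-screen phase |

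The Immediate post-therapy phase places the second avoidance test alongside the 10-minute recording, so some VRET participants may be wearing the band during that test. There is no pre-test or pamphlet counterpart.

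**2. Safeguards in the protocol.** The 2-minute training phase addresses novelty (orientation) only, and it comes after the baseline recording. The 10-minute baseline allows some settling, but the therapy session is planned at 150 minutes.

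**3. The plan's own figure.** The protocol gives no effect, SD or sample size for HR. Its sample size concerns MDAS: difference 6, SD 4.22, type I error 0.05 (taken as two-sided), power 0.9. The noncentral t gives power 0.887 with 11 per arm and 0.914 with 12, so 12 per arm reproduces, and 12 × 1.25 = 15. These supply only the numbers of participants used below.

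**4. Chance of a significant fall when VRET adds nothing (assumed falls).** Let δ be the non-specific fall in SDs of the within-person change. The two-sided 0.05 paired test has noncentrality δ√n on n − 1 degrees of freedom; for δ = 0.5 and n = 15 this is 0.5 × √15 = 1.94.

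| δ | n = 15 | n = 12 |
|---|---|---|
| 0 | 0.05 | 0.05 |
| 0.2 | 0.11 | 0.10 |
| 0.5 | 0.44 | 0.35 |
| 0.8 | 0.82 | 0.71 |
| 1.0 | 0.95 | 0.88 |

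**5. What a between-arm comparison would do.** The expected difference in change is the VRET effect plus (non-specific change in VRET − non-specific change in pamphlet). If the two non-specific changes are equal, the bracket is zero and the error rate returns to 0.05. If they differ, the remainder is bias.

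**6. Its precision.** With noncentrality d√(n/2) on 2n − 2 degrees of freedom, two-sided 0.05:

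- 15 per arm: d = 1.06 SD at 80% power, 1.23 SD at 90%.
- 12 per arm: d = 1.20 SD at 80% power, 1.39 SD at 90%.
- 95% interval half-width with 15 per arm: 2.048 × √(2/15) = 0.75 SD of the change.

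**The case against.** The strongest reply is that the one-arm scope is deliberate and declared. The Abstract words the HR aim as arousal in VRET participants, Table 1 says the measure belongs to that arm, and a pamphlet reader has no in-session response to VR cues. Efficacy rests on MDAS, DFS and VAS-A, which are compared between randomised arms. This stands. Describing HR during exposure and correlating it with presence need no control arm. For %HR at first exposure, settling would hide arousal rather than create it. Repeated meetings with the same VR cue are the treatment itself, not a nuisance. Data analysis also words habituation cautiously.

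None of this covers hypothesis (b), which names VRET as the cause of a reduction after therapy.

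A reader might go further in three ways that the documents do not support:

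- *HR is the trial's only objective measure, so randomisation is wasted.* Table 2 does give HR the objective label, but observer-rated tolerance in the avoidance test is taken in both arms and listed as primary.
- *Recording both arms would make drift cancel.* The VRET session is planned at 150 minutes; pamphlet participants read three pages in the screening area for an unstated time. Time-in-chair effects need not be equal.
- *Mean HR over all five situations would be a sound outcome.* The test records whether each situation is tolerated. A participant who stops early has no such mean, and one who reaches the drill only after therapy could show a higher post-test mean because of improvement.

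**Conclusion.** The point holds for hypothesis (b) and for reading a decline over exposures as evidence that therapy works. As designed, a fall in HR across exposures or after therapy is compatible with VRET, with settling, or with both. It does not reach the primary outcomes, the in-session description of HR, or the presence–%HR correlation.

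The size cannot be fixed from the document. Over assumed non-specific falls of 0.2 to 1.0 SD of the change, the chance of a significant within-arm fall with 15 participants and no VRET effect runs from 0.11 to 0.95. The protocol does not show that such a fall will occur; the calculation shows only that the design could not recognise it.

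**What to change.** **Minimum change.** Restate hypothesis (b), and the habituation sentence in Data analysis, as descriptive within-arm process data that do not support a VRET effect on arousal. This costs only wording.

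**If a VRET effect on HR is to be claimed:**

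- Record HR with the existing band during the pre- and post-intervention avoidance tests in both arms.
- For each participant, take the change in HR (post minus pre) over the situations completed at both tests, and compare it between arms. A situation reached only after therapy then cannot enter one side of the change alone. Report tolerance separately, because the number of situations completed can itself respond to treatment.
- Keep the interval between the two tests similar in both arms where feasible. Otherwise state that time-in-chair effects may not fully cancel.
- Make it a secondary outcome, reported with a confidence interval.

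**Cost.** No extra visit or staff, and the band and receiver are already on site. Fifteen more participants wear the band. The log must run outside the VR session, which needs some set-up because the band is integrated with the VR software and logged through its interface. A resting reference, if wanted, adds the 10 minutes used in the Baseline phase. With 15 per arm the estimate will be imprecise.
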